##### Insomnia

Insomnia Severity Index (ISI) is a 7-item self-report questionnaire assessing the nature, severity, and impact of insomnia [43,44] and will be administered to survivors. Items are rated on a 5-point Likert scale (0=no problem; 4=very severe problem). The scale is scored using a total sum ranging from 0 to 28 and cut scores are interpreted as such: absence of insomnia (0-7), subthreshold insomnia (8-14), moderate insomnia (15-21), and severe insomnia (22-28). The ISI is a reliable and valid measure used to detect cases of insomnia in a population sample and is sensitive to treatment response in patients presenting with sleep difficulties [43].

##### Catastrophizing About Child’s Pain

The Pain Catastrophizing Scale–Parent Version [45] is a 13-item measure used to assess parents’ catastrophic thoughts and feelings about their child’s pain and will be administered over the internet via REDCap. Parents rate statements about their child’s pain on a 5-point Likert scale (ie, “When my child has pain, I can’t keep it out of my mind”). Items are summed to yield a total score and can also be summed to provide scores on 3 subscales: rumination, magnification, and helplessness. Lower scores indicate less catastrophizing. This scale has been found to have good reliability in parents with children who experience pain.

##### Parental Responses to Child’s Pain Behaviors

The Adult Responses to Children’s Symptoms [46,47] measures parental responses to their child’s pain behaviors and will be administered over the internet via REDCap. This study will only use the Protect subscale, which assesses parents’ responses that either positively or negatively reinforce pain complaints. Parents’ responses are rated on a 5-point scale (0=never, 4=always). Subscale scores represent an average of the items, with higher scores indicating more frequent use of that behavioral style. This scale has demonstrated reliability and validity for use with parents of children with chronic pain [46,47].

##### Parent Distress

The Kessler Psychological Distress Scale [48] will be administered to parents and is a 6-item measure used to assess nonspecific psychological distress representing diagnoses of major depression and generalized anxiety disorder and also contains a positive affect domain. The measure has good precision in the 90th-99th percentile range of the population, and has solid psychometric properties across major sociodemographic populations distribution in the United States and Canada [48]. It also strongly discriminates between meeting and not meeting diagnostic thresholds for psychological disorders [48].

### Data Analysis

#### Quantitative Data Analysis

To address objective 1, we will use frequencies and descriptive statistics to describe recruitment and retention rates, treatment adherence, and acceptability. To address objectives 2 and 3, primary efficacy end points of the study will be calculated as within-person changes in outcome measures using Cohen *d* effect sizes from T0 to T1 and T2. Outcome data will be analyzed using paired samples *t* tests in order to assess changes in outcome variables over time. Treatment effect sizes (Cohen *d*) will be calculated for changes in means, standardized by the pooled SD. All quantitative analyses will be conducted using SPSS (version 27; IBM Corp).

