**Methods:**

A single-arm mixed methods pre-post intervention study design will be used. Participants will be 34 survivors and at least one of their parents or caregivers. Inclusion criteria are (1) a cancer history, (2) current age of 10-17 years, (3) >2 years post treatment or >5 years post diagnosis, (4) pain present over prior 3 months impairing >1 area of daily life and occurring >1 time per month, and (5) computer access with broadband internet. Survivors will complete a pretreatment questionnaire, which will include the following: the Child Activity Limitations Interview, the pain intensity Numerical Rating Scale, Patient-Reported Outcomes Measurement Information System (PROMIS)–Pain Interference, Anxiety, Depression, Insomnia Severity Index, and Adolescent Sleep Wake Scale. Parents will complete the Pain Catastrophizing Scale–Parent Version and the Adult Responses to Child Symptoms. Upon completion of pretreatment questionnaires (T0), survivors will begin WebMAP. After the 8-week intervention, survivors will complete the same measures (T1), and at 3-month follow-up (T2). Posttreatment interviews will be conducted to determine acceptability. Feasibility will be assessed via recruitment and retention rates. Treatment engagement will be measured by number of modules completed. Pre-post outcome data will be assessed using linear mixed models. Qualitative data will be analyzed using thematic analysis. Patient partners will be involved in study design, recruitment, interpretation of results, and knowledge translation.

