##### Feasibility

Feasibility will be assessed by considering rates of: (1) recruitment, (2) retention, (3) treatment engagement, (4) acceptability, and satisfaction. “Recruitment” will be measured by the number of survivors enrolled or consented divided by the total number of survivors invited to participate. Based on previous trials of similar nature [17], a 50% recruitment rate of eligible survivors will be used as the benchmark to determine this factor of study feasibility. “Retention” will be measured by the number of survivors who complete the study defined as those who complete the intervention and all assessments from enrollment (T0) to 3-month follow-up (T2) divided by the total number of survivors who enrolled in the study. Survivors will be considered to be enrolled in the study when they have read and signed the informed consent form. Based on previous pilot trials [17], an 80% retention rate will be considered “feasible.” “Treatment engagement” will be measured by number of modules completed by survivors and parents. Based on similar trials [17], the goal to determine treatment engagement will be at least 75% of survivors completed at least 6 of the 8 modules, and the mean number of modules completed by the sample being at least 6. We hypothesize that >75% of survivors will complete assessment measures across the 3 specified time points. “Acceptability” will be measured using the Treatment Evaluation Inventory—Short Form (TEI-SF) [32], a 9-item self-report measure of acceptability of treatment, completed by both survivors and parents. The TEI-SF was originally designed to measure parents’ acceptability of a treatment for children with problem behaviors but has been adapted to assess the acceptability of WebMAP in previous studies [17]. Responses are scored on a 5-point Likert scale and summed to create a total score. Higher scores represent better acceptability. Moderate to high acceptability, defined as a score of 27 or higher, has been considered sufficient for trials of similar nature [17,33]. The TEI-SF has good reliability and validity across various child treatments [32]. This study will use the adapted version and will be completed by survivors and parents.

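### The abstract and the Methods name different analyses for the same pre-post outcomes (linear mixed models against paired t tests), and the objectives are numbered inconsistently

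*Protocol article*

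**What the plan says.** **Method.** The abstract of the protocol article, under Methods, says: "Pre-post outcome data will be assessed using linear mixed models". The Quantitative Data Analysis section says: "Outcome data will be analyzed using paired samples" t tests, with Cohen d as "effect sizes from T0 to T1 and T2", "standardized by the pooled SD". That section does not mention a mixed model, and the abstract does not mention a t test.

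**Expected loss.** The Sample Size section recruits 38 to end with 34, allowing 10% attrition. The Feasibility section says "an 80% retention rate will be considered" feasible. It counts a survivor as retained only if both the intervention and every assessment through T2 were completed. It adds: "We hypothesize that >75% of survivors will complete assessment measures across the 3 specified time points".

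**Objectives.** In the abstract and at the end of the Introduction, objective 2 is the qualitative work, objective 3 the survivor outcomes and objective 4 the parent outcomes. In the Measures section, the Objective 2 heading covers every quantitative outcome scale, survivor and parent alike, and the interviews come under Objective 1. The analysis section opens its efficacy text with "To address objectives 2 and 3, primary efficacy end points of the study".

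**The concern.** Both texts fix a method for the same outcomes, and the methods differ. This is not detail left to a fuller document: whichever text that document follows, it contradicts the other. Until one is chosen, the analyst can choose after seeing the data.

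With three time points and expected loss, the choice can affect the result. Paired t tests may base T0–T1 and T0–T2 on different subsets. Their estimates describe all enrolled survivors only if loss is unrelated to the change being measured. The Discussion makes the move to a phase III trial depend partly on promising preliminary efficacy, so an overstated change among those who stay could feed that decision. The Discussion also anticipates that milder pain may reduce motivation to engage, so loss related to pain is not far-fetched.

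The numbering conflict adds doubt about which outcomes the analysis sentence covers.

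**Working it through.** **1. The plan's own figures.** Recruitment: 34 / (1 − 0.10) = 37.8, rounded up to 38, which reproduces. Power: for a two-sided paired t test at α = 0.05, df = n − 1 and noncentrality = dz × √n, where dz is the change divided by the SD of change. With dz = 0.4 and n = 34, power is 0.62, not 0.80. The stated 80% is reached if d is standardised by the pooled SD and the T0–follow-up correlation ρ is about 0.67: dz = 0.4 / √(2 × (1 − 0.67)) ≈ 0.49. The article gives no correlation. That is a separate matter and the present point does not depend on it.

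**2. How many pairs could be lost.**

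| Basis | Calculation | Left of 38 |
|---|---|---|
| Budgeted attrition, 10% | 38 × 0.90 = 34.2 | about 34 |
| Retention benchmark, 80% | 38 × 0.80 = 30.4 | about 30 |

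The second row is an upper guide to T2 loss at the benchmark. A survivor who skips modules, or misses only T1, is not retained but still supplies a T0–T2 pair.

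**3. Power.** Two-sided, dz = 0.4:

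| Complete pairs | Power |
|---|---|
| 38 | 0.67 |
| 34 | 0.62 |
| 30 | 0.56 |

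Even with no loss, power is only 0.67. With 30 complete cases and 8 missing only T2 completely at random, a mixed model gives about 0.59 to 0.62. The choice of method therefore accounts for roughly 3 to 6 points.

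**4. Completely random loss.** Simulation with 38 survivors, 8 of them lacking T2, and scores with SD 1. The likelihood estimate regresses T2 on T0 and T1 among those observed and averages the prediction over everyone.

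| Correlations assumed | SE, complete pairs | SE, likelihood | Reduction |
|---|---|---|---|
| All 0.5 | 0.183 | 0.178 | about 3% |
| T0–T1 0.6, T1–T2 0.7, T0–T2 0.4 | 0.200 | 0.188 | about 6% |

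Neither estimate is biased. The complete-pair SE follows directly: √(2 × (1 − 0.4)) / √30 = 1.095 / 5.477 = 0.200.

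**5. Loss that depends on observed scores.** Large-sample simulation with correlations 0.6 / 0.7 / 0.4, true T0–T2 change −0.40 SD and 20% T2 loss. The log-odds of loss rise by 0.5, 1.0 or 1.5 per SD of the driver.

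| Loss driven by | Complete pairs (slope 0.5 / 1.0 / 1.5) | Overstatement | Likelihood estimate |
|---|---|---|---|
| Worse T1 score | −0.41 / −0.42 / −0.43 | 0.01 to 0.03 SD | −0.40 |
| Poor T0–T1 change | −0.48 / −0.54 / −0.58 | 0.08 to 0.18 SD | −0.40 |

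Against an SE of about 0.20 SD, the first range is at most 0.03 / 0.20 = 15% of one SE. The second is 40 to 90% of one SE (0.08 / 0.20 to 0.18 / 0.20).

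**6. Objective numbering, side by side.**

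| Place | Qualitative work | Survivor outcomes | Parent outcomes |
|---|---|---|---|
| Abstract; end of Introduction | 2 | 3 | 4 |
| Measures headings | 1 | 2 | 2 |
| Quantitative Data Analysis | not numbered | 2 and 3 | not named separately |

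**The case against.** The contradiction itself cannot be defended. The case on the other side is that its consequences are modest.

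- **Secondary outcomes.** The trial registration table lists feasibility and satisfaction as primary outcomes and the symptom and parent scales as key secondary. Objective 1 is descriptive and unaffected. This stands and limits the severity.
- **Power.** A reader might take 56% power at 30 pairs as the price of the t test. The figures do not support that. Power is already 0.62 at 34 and 0.67 at 38, so the shortfall comes mainly from the sample size, and no model recovers missing scores.
- **Amount of loss.** A reader might state as fact that 8 of 38 will be lost. The 80% is a feasibility benchmark, retention also requires finishing the intervention, and the plan's own attrition figure is 10%.
- **Direction of bias.** The article gives no dropout mechanism and no correlations, and does not say that those who stay do better. The bias figures are scenarios, and the larger range arises only if loss follows a poor early change. With complete data the two methods estimate the same mean changes.
- **Parent outcomes.** A reader might infer that these are assigned no analysis. The Measures section places the parent scales under Objective 2, and the t-test sentence is not limited to survivors. They are misnumbered, not left out.

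What remains is that two methods are fixed for the same outcomes, and they can differ whenever follow-up is incomplete.

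**Conclusion.** The point holds as a should-fix. The abstract and the Methods prescribe different analyses for the same pre-post outcomes, and the objective numbers in the Measures and analysis sections do not match the stated list. Both follow from the text alone and need no assumption.

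The size of the consequence does rest on assumptions. With up to 20% of T2 scores missing, the mixed model gains about 3 to 6% in standard error under completely random loss. It avoids a bias of about 0.01 to 0.03 SD if loss follows the T1 score, or about 0.08 to 0.18 SD if it follows a poor T0–T1 change. It protects when loss depends on observed scores, not when it depends on the unobserved T2 score itself. The argument for the mixed model is a single pre-specified method and protection against bias, not rescue of power.

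**What to change.** 1. In Quantitative Data Analysis, name the abstract's linear mixed model as the analysis of survivor outcomes: time as a factor (T0, T1, T2), all survivors with a T0 score, and T1–T0 and T2–T0 contrasts with 95% confidence intervals. Covariance structure and degrees-of-freedom method can be left to the statistical analysis plan.
2. Keep the paired t tests as a sensitivity analysis, and report the number of pairs in each.
3. State the analysis of parent outcomes for the time points at which parents are assessed. The Data Collection section gives parents the battery at T0 and T1 and mentions only survivors at T2.
4. Change the reference to objectives 2 and 3 in the analysis text to objectives 3 and 4, and make the Measures headings consistent with the stated list.

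The cost is wording and slightly more analysis work. SPSS, already named, fits the model. No change to data collection or sample size is needed.

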#### Qualitative Data Analysis

Qualitative data will be coded independently by 2 study team members and analyzed using reflexive thematic content analysis, consistent with Braun and Clark’s thematic analysis guide [49]. Team members will first familiarize themselves with the data by reading the transcripts multiple times. The data will then be coded independently using a hybrid deductive-inductive approach whereby codes will be inductively derived from the data and codes will be deductively generated from existing literature [50]. Afterward, the 2 coders and the principal investigator (MP) will meet to discuss the codes and iteratively generate themes and subthemes. Additional team members will be invited to offer critical reflections and insight on the interpretations. Several strategies will be used throughout the data analysis to enhance rigor including having clear and extensive descriptions around the research setting and process, member checking, providing thick descriptions of themes, regular debriefing meetings, data triangulation with the quantitative analysis, and having the authors actively practicing reflexivity through notes and meetings [51].

### Ethics Approval

Ethics approval was obtained from the Health Research Ethics Board of Alberta Cancer Committee (HREBA.CC-21-0272). Any changes to this protocol will be made through this ethics board. Potential survivors will be contacted and informed of study details such as the voluntary nature of participation, confidentiality, and risks and benefits of participating. Once survivors are fully informed, they will be given the opportunity to provide written consent and enroll in the study. Survivors will provide assent and will require parental consent to participate. Parents will provide consent for their own participation. WebMAP is known to be safe and previous trials reported no adverse events directly related to study participation [17]. Data will be collected using participant identification numbers to protect confidentiality. Names and corresponding identification numbers will be kept in a separate, password-protected document. Potential benefits of participating in the intervention include a reduction in pain and an improvement in mental health.

The results will be disseminated to a range of stakeholders such as survivors of childhood cancer, parents of survivors of childhood cancer, health care practitioners, and researchers. Dissemination efforts will be made through national and international conference presentations, social media posts (eg, Twitter and Facebook), peer-reviewed academic journal publications, and cancer advocacy group newsletters (eg, Kids Cancer Care).

## Results

This study was funded in January 2022. Data collection started in June 2022 and is projected to finish by August 2023. As of December 2022, we have recruited 10 participants, with zero participants completing all aspects of the protocol.

## Discussion

The primary objective of this study is to assess the feasibility and acceptability of a well-studied internet-based psychological intervention developed for adolescents with chronic pain in a population of youths with a history of cancer. The strength of the study is the usage of a mixed methods design, which will provide both quantitative and qualitative information regarding the feasibility, acceptability, and potential efficacy of the intervention. Additionally, 3 patient and caregiver partners with lived experience of cancer and chronic pain will inform the study from the beginning. The web-based intervention will also be accessible for survivors who would not otherwise be able to access CBT with a psychologist. This may prove to be more inclusive for survivors living in rural or remote areas and survivors of families with low household incomes.

The proposed study has limitations. Participants for previous studies were recruited from tertiary pain clinics, which serve the most severe cases of chronic pain. One limitation of this study is that the participants may not experience a severe chronic pain problem compared to participants from other studies, though screening criteria require that they have chronic pain that affects at least one area of their daily life, similar to previous studies. This limitation may lead to smaller effects of the pain intervention on participants with mild to moderate chronic pain problems, and may also affect motivation to engage in the program if participants are generally functioning with pain. Another limitation is that the study will be conducted at a single location, in which the feasibility and acceptability of the study may not be generalizable to survivors across Canada.

The Obesity-Related Behavioral Intervention Trials (ORBIT) Model for Behavioral Treatment Development [52] is a framework for increasing the number of optimized evidence-based behavioral trials to prevent and treat chronic diseases. The ORBIT model includes several phases that serve as a roadmap for conducting behavioral intervention research in a systematic way that ensures quality and cost-efficient methods. This dynamic framework begins with a significant clinical question. This study proposes that while chronic pain is a prevalent issue in survivors of childhood cancer, no interventions to date have been empirically tested on this population. Phase I in the ORBIT Model represents the Design phase, where the goal is to design essential features of the intervention or to adapt to an existing treatment [52]. This phase has already been completed in that the intervention has been designed, refined, and tested on a different population [17]. Phase II represents the Preliminary Testing phase, where the goal is to test the ability of a fixed intervention to produce a clinically significant improvement on a behavioral risk factor [52]. While this phase has already been completed in previous studies [17], this intervention has never been tested on adolescents with a history of cancer, and thus this study aims to complete this phase. Should survivors not find the study helpful and adjustments are warranted, the trial will move back to phase I to be tailored for youths with a history of cancer. If the study finds WebMAP to be feasible and acceptable with promising preliminary efficacy, the trial will move to a phase III efficacy trial in future studies. This study will provide valuable information about the potential usefulness of WebMAP for survivors of childhood cancer with chronic pain.

## Abbreviations

CALI: Child Activity Limitations Interview
CBT: cognitive behavioral therapy
ISI: Insomnia Severity Index
ORBIT: Obesity-Related Behavioral Intervention Trials
PROMIS: Patient-Reported Outcomes Measurement Information System
REDCap: Research Electronic Data Capture
TEI-SF: Treatment Evaluation Inventory—Short Form
WebMAP: web-based management of adolescent pain
